**Methods and analysis:**

The study will enroll over 4,000 confirmed COVID-19 patients from Gansu Provincial Hospital, treated from December 2022 to May 2023, as the baseline. These patients are spread across 14 cities in Gansu Province, with geographic coordinates ranging from 92°13′E to 108°46′E and 32°31’N to 42°57’N. Follow-ups will be conducted via structured telephone interviews at 24, 36, and 48 months post-discharge, from 2024 to 2027, to assess PASC and long-term health outcomes. Participants will be categorized into three age groups: children and teenagers (birth to 18 years), adults (18–65 years), and the older adult (over 65 years). Environmental and socioeconomic data corresponding to each case are also integrated. The primary objective is to assess the persistence and long-term health outcomes of PASC symptoms. Secondary objectives focus on evaluating the acute infection phase, its progression, and the efficacy of medical management strategies in influencing PASC trajectories. Mixed-effects models will be utilized to evaluate the impact of various factors on PASC, while spatiotemporal analyses will explore the correlations between environmental and socioeconomic conditions and the diagnosis and recovery trajectories of PASC.

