### Statistical analysis

A variety of statistical methodologies will be employed to analyze the primary and secondary outcomes in this study. The data analysis begins with descriptive and inferential statistical methods to identify patterns and establish correlations. Continuous data will be presented as means with standard deviations (SD), while categorical variables will be reported as percentages. For comparisons across groups, analysis of variance (ANOVA) will be used for continuous variables, and chi-square tests for categorical variables, both with Bonferroni corrections applied in post-hoc analyses. A significance level of *p* < 0.05 will be consistently applied, with adjustments made for multiple comparisons to enhance the reliability of results. Logistic regression models will be employed to evaluate the impact of multiple factors on the severity of PASC. We will utilize a multivariable logistic regression model to analyze the relationship between various independent variables, including demographic factors, clinical characteristics, and environmental exposures, and the binary outcome of PASC presence or absence. The model will integrate variables selected based on clinical relevance and statistical significance derived from preliminary univariate analyses, ensuring that only factors significantly associated with the outcome are included in the final analysis. Variables for inclusion will be chosen based on their potential impact on PASC, informed by both clinical judgment and empirical evidence from initial analyses. We plan to investigate interaction terms, particularly between key demographic and clinical variables, to explore complex interactions that may affect PASC risk. Model fit will be assessed using the Hosmer-Lemeshow test for goodness-of-fit and Receiver Operating Characteristic curve analysis to evaluate predictive accuracy. We will also employ validation techniques such as split-sample validation or cross-validation to confirm the model’s robustness. Sensitivity analyses will be conducted to examine the stability of our results under various assumptions regarding data missingness and potential measurement errors, ensuring that our findings are reliable and applicable across different scenarios. Additionally, advanced analytical techniques will complement these methods, utilizing R (version 4.3.0) with the ‘gpboost’ and ‘stats’ packages and Python (version 3.10) with ‘sklearn’ and ‘gpboost.’

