## Discussion

This study will employ a longitudinal design to investigate how environmental, socioeconomic, and clinical factors shape PASC outcomes in a demographically diverse population. Comprehensive health data collected during the initial COVID-19 hospitalization help distinguish pre-existing conditions from symptoms emerging as part of PASC. By integrating these clinical records with environmental and socioeconomic variables through mixed-effects models and spatiotemporal analyses, the research provides a comprehensive understanding of how both internal factors (e.g., individual health status, comorbidities) and external factors (e.g., air quality, socioeconomic conditions) influence long-term health outcomes following COVID-19. To ensure a representative sample, the cohort is stratified by age, sex, and initial symptom severity, allowing for a detailed and subgroup-specific analysis of PASC manifestations. This multidimensional approach is essential for uncovering the complex interactions between patient-level susceptibility and broader external influences, ultimately informing targeted strategies to improve the management and mitigation of long-term COVID-19 effects.

Existing literature has widely documented the potential influences of underlying comorbidities, demographic factors, and environmental conditions on PASC outcomes (64). Pre-existing conditions such as cardiovascular disease, diabetes, and chronic respiratory disorders have been shown to exacerbate the severity of PASC symptoms, leading to prolonged recovery and an increased risk of complications (65). Individuals with chronic illnesses are more likely to experience severe acute COVID-19, which may predispose them to long-term sequelae due to sustained systemic inflammation and immune dysregulation (66). For instance, patients with diabetes and obesity have demonstrated heightened susceptibility to persistent inflammatory states post-COVID-19, contributing to ongoing fatigue, dyspnea, and cardiovascular dysfunction (67, 68). By examining how pre-existing health conditions interact with PASC, this study aims to elucidate the mechanisms through which chronic illnesses impact recovery trajectories and to identify potential intervention strategies.

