A key strength of this study is its extended follow-up period of up to 48 months post-discharge, allowing for a comprehensive assessment of long-term PASC progression and persistence across different age groups. This prolonged observation provides valuable insights into age-specific recovery patterns, refining predictive models for long-term health outcomes and facilitating the development of targeted interventions. Additionally, the use of Geographic Information Systems (GIS) enhances the study by generating disease distribution maps, which help identify environmental and geographic factors associated with PASC. These insights are not only essential for detecting high-risk areas but also for guiding individualized patient care strategies.

Beyond mapping geographic influences, the integration of environmental and socioeconomic data with clinical outcomes strengthens the understanding of how external factors, such as air pollution, economic disparities, and urbanization, affect the severity and trajectory of PASC. Identifying these factors has direct implications for patient care, enabling healthcare providers to incorporate external influences into personalized treatment plans. Time-series analyses further enhance this approach by tracking temporal trends and evaluating the effects of environmental changes on health outcomes, providing a dynamic perspective on how fluctuating conditions contribute to disease progression. Meanwhile, causal inference models help establish robust causal relationships between environmental, socioeconomic, and clinical variables, ensuring a more rigorous evaluation of COVID-19’s long-term effects on PASC. By combining these analytical techniques, the study offers a multidimensional framework for understanding how environmental and socioeconomic conditions interact with individual health factors, ultimately informing more precise treatment and intervention strategies. This research also carries significant implications for patient care, particularly in identifying specific risk factors that exacerbate PASC in vulnerable populations. By considering both internal and external determinants of health, this study supports a shift toward precision medicine, ensuring that interventions address not only biological vulnerabilities but also environmental and socioeconomic disparities that influence recovery.

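### Fit of the PASC logistic model is judged by the Hosmer-Lemeshow test, whose verdict depends on the number analysed; no named measure shows the size of miscalibration

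*Protocol article*

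**What the plan says.** The Statistical analysis section of the protocol article plans a multivariable logistic model for "the binary outcome of PASC presence or absence". On checking that model it states: "Model fit will be assessed using the Hosmer-Lemeshow test for goodness-of-fit and Receiver Operating Characteristic curve analysis to evaluate predictive accuracy". On the threshold it states: "A significance level of *p* < 0.05 will be consistently applied". Split-sample validation or cross-validation is added to confirm robustness, without saying what will be measured on the held-out data.

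On size, the Abstract says: "The study will enroll over 4,000 confirmed COVID-19 patients". The article gives no expected PASC prevalence, no expected number analysed and no age-group sizes. It does not say how many groups the Hosmer-Lemeshow test will use, or what follows if the test is significant.

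**The concern.** Calibration asks whether predicted risks agree with observed frequencies, and by how much they miss. Of the checks named, only the Hosmer-Lemeshow test bears on it. The ROC curve is unchanged by any strictly increasing transformation of the predicted risks, so a model can have a good ROC area and be badly calibrated. A resampling scheme without a metric does not settle the matter.

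The Hosmer-Lemeshow test returns a p-value. For a fixed degree of misfit, the chance of p < 0.05 rises with the number of patients. The result therefore mixes two things that a reader needs separately: how wrong the predictions are, and how much data there was to show it. At stake is how the fit of this model is described. The same miscalibration could be reported as poor fit in a large analysis set and as acceptable fit in a smaller one.

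**Working it through.** The article contains no power or threshold figure for this test, so there is nothing to reproduce. The check asks how the verdict changes with n when the misfit is held fixed.

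**Inputs from the article:** significance level 0.05; binary outcome; cohort over 4,000 (4,000 used).

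**Assumptions:** 10 risk groups, so 8 degrees of freedom and a critical value of 15.51. Prevalence 10% to 50% in the analytic check and about 30% in the simulation. Analysed n of 2,800 (70% of 4,000) after attrition, and of 300 for a small analysis set.

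**1. Analytic check.** Suppose the predicted risk is wrong by the same absolute amount d in every decile, and use the overall prevalence p for the variance. The statistic is then approximately noncentral chi-square with 8 degrees of freedom and noncentrality

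λ = n·d² / [p(1−p)].

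At n=4,000, p=0.30 and d=0.01: λ = 4,000 × 0.0001 / 0.21 = 1.90, which gives a rejection probability of 13%. With d=0.02: λ = 7.62, which gives 45%. Across prevalences at n=4,000:

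| Prevalence | 1-point error rejected | 2-point error rejected |
|---|---|---|
| 10% | 26% | 87% |
| 20% | 16% | 59% |
| 30% | 13% | 45% |
| 50% | 11% | 38% |

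Rejection reaches 50% at λ = 8.40, so the error rejected half the time is d = √[8.40·p(1−p)/n]. At p=0.30 this is 2.1 points for n=4,000, 2.5 points for n=2,800 and 7.7 points for n=300. At n=4,000 it runs from 1.4 points (prevalence 10%) to 2.3 points (prevalence 50%). The ratio between two sample sizes does not depend on prevalence: √(4,000/2,800) = 1.2 and √(4,000/300) = 3.7.

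**2. Simulation.** True model: logit P = −0.95 + 0.6x + 0.4z + q(x²−1), with x and z standard normal and prevalence about 30%. The fitted model omits the quadratic term. The test uses 10 groups at 5%. Share of samples rejected:

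| q | Mean decile error (worst decile), points | n=4,000 | n=2,800 | n=300 |
|---|---|---|---|---|
| 0.10 | about 1.1 (2.8) | 24% | 19% | 6–7% |
| 0.15 | about 1.6 (4.1) | 56% | 38% | 8% |
| 0.20 | about 2.2 (5.5) | 87% | 71% | 9–11% |
| 0.30 | about 3.4 (8.4) | nearly 100% | 98% | 16–20% |

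With no misfit (q=0) rejection is about 4% to 6% at each size, so the test behaves properly under a correct model. Repeat runs differ from the single figures shown by up to about 4 percentage points.

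Each row has one degree of misfit and several verdicts. In the last row, a model whose worst decile is wrong by about 8 points almost always fails at 4,000 and passes in at least four of five samples of 300.

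**The case against.** Power that rises with n is a property of every test, and the Hosmer-Lemeshow test is standard. The article is condensed and may leave calibration plots to the full protocol or analysis plan; it does not exclude them. The simulated models really are misspecified, so rejecting them is correct detection, and whether a 2-point error matters is a judgement for which the article gives no tolerance. These points keep the severity low. They do not remove the point, because the article states which instrument judges fit, and that instrument cannot say whether an error is large enough to matter.

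Four stronger readings are tempting, and the documents do not support them:

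- **That the test at 4,000 patients rejects any model with an average error of 1 to 2 points.** It does not. A uniform 1-point error is rejected only 11% to 26% of the time for prevalence 10% to 50%, and a 1.1-point mean error in the simulation about 24% of the time. The number analysed will probably be below 4,000, since the Study population section excludes patients who die, decline or cannot be reached. That lowers rejection further.
- **That badly calibrated models will be passed in a small age group.** The article defines three age groups and speaks of "allowing for a detailed and subgroup-specific analysis of PASC manifestations", but it states no separate logistic model and no Hosmer-Lemeshow test by age group. The 300 is an illustration.
- **That a model will be accepted or discarded on the p-value.** No consequence is stated.
- **That miscalibrated risks will reach individual care.** The Discussion speaks of "refining predictive models for long-term health outcomes and facilitating the development of targeted interventions" and credits this to long follow-up. No section says that predicted risks from this logistic model will be used for individual patients.

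**Conclusion.** The point holds as a minor one. The calibration of the logistic model rests on a test whose verdict tracks the number analysed, and no named measure reports how large the miscalibration is. A mean decile error of 2.2 points is rejected about 87% of the time at 4,000, 71% at 2,800 and roughly 10% at 300. Those percentages depend on the assumed 30% prevalence, the single form of misfit and the assumed analysis sizes. The dependence on n does not: the detectable uniform error differs 3.7-fold between 4,000 and 300 patients at any prevalence. It follows that a non-significant result should not be read as good calibration, nor a significant one as an error that matters. The primary outcome is not affected.

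**What to change.** In the Statistical analysis section, base the calibration assessment on the calibration intercept, the calibration slope and a smoothed calibration curve with a 95% band; the Brier score is optional. Compute them on held-out predictions from whichever planned validation is used, split-sample or cross-validation, and name that choice. Report them overall, and by age group if models or predictions are reported by age group. Keep ROC area as the measure of discrimination. The Hosmer-Lemeshow test may be reported alongside but should not decide fit.

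The cost is a sentence or two in the plan and a small amount of extra analysis with standard software. No new data are needed.

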#### Generalized linear mixed-effects models (GLMM) for risk factor estimation

To estimate the influence of risk factors on PASC, Generalized Linear Mixed-Effects Models (GLMM) will be applied. These models will allow for a quantitative assessment of how various environmental and individual-level risk factors contribute to PASC, while controlling for potential confounders. A random intercept for each city will be included to account for non-measurable inter-city variability. Interaction terms between individual and environmental factors will be constructed, with only those demonstrating statistical significance and theoretical or empirical relevance retained for further analysis.

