## Methods and analysis

### Study population

This prospective cohort study, will enroll over 4000 individuals with RT-PCR-confirmedSARS-CoV-2 at baseline, hospitalized at Gansu Provincial Hospital in China from December 2022 to May 2023 (Gansu PASC dataset). Aligning with methodologies from other PASC research, we will gather comprehensive health data during the patients’ initial hospitalization due to COVID-19 (31). The data collection will include extensive hospital records from their acute COVID-19 admissions, capturing demographic information, clinical data, comorbidities, pre-existing symptoms, and other relevant health details.

The patients were from all 14 cities in Gansu Province (92°13′E-108°46′E, 32°31’N-42°57’N), with various environmental and socioeconomic backgrounds. The municipal geographic coordinates of the 14 cities are detailed as follows: Lanzhou (103°51′E, 36°3’N); Jiayuguan (98°23′E, 39°80’N); Jinchang (102°19′E, 38°52’N); Baiyin (104°14′E, 36°55’N); Tianshui (105°72′E, 34°58’N); Wuwei (102°64′E, 37°93’N); Zhangye (100°45′E, 38°92’N); Pingliang (106°66′E, 35°54’N); Jiuquan (98°49′E, 39°73’N); Qingyang (107°64′E, 35°71’N); Dingxi (104°59′E, 35°61’N); Longnan (104°96′E, 33°37’N); Linxia Hui Autonomous Prefecture (103°21′E, 35°60’N) and Gannan Zang Autonomous Prefecture (102°91′E, 34°98’N). Baseline data will be collected using hospital records, and follow-up assessments will be performed at 24-, 36-, and 48-months post-discharge via structured telephone interviews (Table 1). Exclusion criteria are limited to individuals without available contact details, those who deceased during hospitalization or follow-up, those who declined to participate, and those unreachable for follow-up assessments.

**Table 1 tab1:** Evaluation parameters at baseline and follow-up visits.

Evaluation parameter	Baseline°	Follow-Up°° (telephone interviews)		
	(Hospital admission)	Visit 1 (24 m)	Visit 2 (36 m)	Visit 3 (48 m)
Informed consent	x			
Inclusion criteria met	x			
Demographics*	x			
Environmental/socio-economic factors†	x			
Symptoms‡	x	x	x	x
Life styles¶	x	x	x	x
Vaccination information**	x			
Reinfection††		x	x	x
Recovery condition‡‡		x	x	x
Comorbidities¶¶	x			
Laboratory test results***	x			
Treatment†††	x			
Clinical outcomes	x			
Medical management‡‡‡		x	x	x
Assessment Tools¶¶¶				
EQ-5D-5L score (Adults)	x	x	x	x
mMRC score (Adults)	x	x	x	x
GAD-7 score (Adults)	x	x	x	x
PHQ-9 score (Adults)	x	x	x	x
FSS score (Adults)	x	x	x	x

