Beyond comorbidities, demographic factors such as gender, education level, and marital status may also influence PASC trajectories (69). Gender differences in immune response and health-seeking behaviors have been linked to variations in symptom persistence and severity, with women more frequently reporting prolonged PASC symptoms, including fatigue, neurological issues, and autonomic dysfunction (70). Additionally, education level and marital status serve as proxies for social support and healthcare access, both of which are critical for managing chronic conditions and facilitating recovery (71). Limited health literacy, often associated with lower education levels, may impact adherence to post-COVID care recommendations, while marital status may influence mental health resilience and access to medical resources (72–74). By incorporating these demographic variables into our analysis, we aim to identify groups with greater susceptibility or resilience to PASC and assess how these interactions affect recovery trajectories.

Environmental pressures, such as air quality, urbanization, and access to green spaces, are increasingly recognized as key determinants of post-COVID-19 health outcomes (15, 20, 75). Air pollution has been linked to increased COVID-19 severity and mortality, and higher exposure to PM2.5 and NO2 has been associated with a higher prevalence of long-term respiratory and cardiovascular symptoms in PASC patients (75). Conversely, access to green spaces has been shown to provide protective benefits, improving mental and respiratory health and facilitating recovery (76). Given the environmental diversity of our study sites, this research will assess how these factors contribute to symptom persistence and recovery, leveraging existing knowledge on environmental determinants of health outcomes to refine analytical approaches and enhance the understanding of PASC progression.

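### Individual-by-environment interactions are screened by significance of product terms, and no absolute-risk measure by subgroup is stated, although the aim is to inform targeted interventions

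*Protocol article*

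**What the plan says.** Two parts of the protocol article plan interaction terms.

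- Statistical analysis: "We will utilize a multivariable logistic regression model" for "the binary outcome of PASC presence or absence", and "We plan to investigate interaction terms, particularly between key demographic and clinical variables". The significance level is also set there: "A significance level of *p* < 0.05 will be consistently applied", with adjustment for multiple comparisons.
- GLMM section: "To estimate the influence of risk factors on PASC, Generalized Linear Mixed-Effects Models (GLMM) will be applied", with a random intercept for city. "Interaction terms between individual and environmental factors will be constructed"; a term goes forward only if it is statistically significant and has theoretical or empirical support. The link function is not given.

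The Introduction names interactions between personal characteristics and environmental risks as the gap to be closed, and gives targeted intervention as the purpose. The Discussion returns to vulnerable populations and intervention strategies.

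The GPBoost section describes a model that can represent higher-order interactions. Its features are pruned by their significance in the GLMM, and results are summarised as mean absolute SHAP values. The Discussion also mentions subgroup-specific analysis of PASC manifestations. The article names no additive measure of interaction and no exposure risk difference within subgroups.

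**The concern.** The retention rule decides which individual-by-environment interactions are pursued. On the logit scale, a product term of zero means that the exposure multiplies the odds of PASC equally in both groups. It does not mean that the exposure causes the same number of extra cases in both. For a common outcome the two can differ widely, and deciding where to target depends on the extra cases.

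Under the stated rule, the study could report no interaction between, say, pollution and comorbidity where reducing the exposure would prevent about twice as many cases per 1,000 people in one group as in the other. Nothing else in the plan is stated to show this.

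**Working it through.** The plan gives no sample-size, power or interaction figure, so there is nothing to reproduce. What follows is an illustration.

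**Inputs from the protocol article.** Cohort: the study "will enroll over 4000 individuals with RT-PCR-confirmedSARS-CoV-2 at baseline" (4,000 used). Significance level 0.05 (two-sided assumed; not stated). Binary outcome.

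**Assumed inputs.** Unexposed PASC risk in a lower-risk and a higher-risk group, the exposure odds ratio (OR), four equal cells, no clustering, and a lower case of 2,400 analysable patients.

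**Step 1: risk differences under a common OR (true product term zero).**
Exposed risk = p·OR / (1 − p + p·OR); risk difference RD = exposed risk − p.

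- p = 10%, OR 2: 0.20/1.10 = 18.2%, RD 8.2 points.
- p = 30%, OR 2: 0.60/1.30 = 46.2%, RD 16.2 points.

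Other cases by the same formula:

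| Unexposed risks | Common OR | RD, lower-risk group | RD, higher-risk group |
|---|---|---|---|
| 5% vs 20% | 2.0 | 4.5 | 13.3 |
| 10% vs 30% | 2.0 | 8.2 | 16.2 |
| 10% vs 30% | 1.5 | 4.3 | 9.1 |
| 20% vs 33.3% | 1.2 | 3.1 | 4.2 |
| 30% vs 60% | 1.5 | 9.1 | 9.2 |
| 50% vs 70% | 2.0 | 16.7 | 12.4 |

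The direction changes because RD = p(1 − p)(OR − 1)/(1 + p(OR − 1)), which peaks at p = 1/(1 + √OR): 41% for OR 2 and 45% for OR 1.5. Below the peak the higher-risk group has the larger absolute effect; above it, the smaller.

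**Step 2: additive interaction in the 10% vs 30%, OR 2 case.**
RERI = RR(both) − RR(exposure only) − RR(group only) + 1 = 4.62 − 1.82 − 3.00 + 1 = 0.80.

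**Step 3: what each test would see in that case.**
The true product term is zero, so at 0.05 it is kept in about 5% of studies, by chance.
For the contrast of risk differences, 16.15 − 8.18 = 7.97 points. With 1,000 per cell, SE = √[(0.0900 + 0.1488 + 0.2100 + 0.2485)/1000] = 0.0264. Then z = 0.0797/0.0264 = 3.02 and power = Φ(3.02 − 1.96), about 86%. With 600 per cell (N = 2,400) it is about 65%. At OR 1.5 with the same unexposed risks, power is 47% and 31%.

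**Step 4: a product term that is small but not zero.**
Risks 10% to 14% and 30% to 40% give ORs of 1.465 and 1.556, ratio 1.06. SE of the log ratio = √[Σ 1/(n·p(1 − p))] = √0.0283 = 0.168, and log 1.06 is about 0.060, so z = 0.36 and power is about 6.5% at N = 4,000. The excess is 40 vs 100 cases per 1,000 exposed.

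**Step 5: do the other analyses fill the gap?**
GPBoost can fit interactions, but its inputs are pruned by GLMM significance, and a mean absolute SHAP value is an overall importance without direction, not a risk difference in a subgroup. The subgroup analysis in the Discussion concerns manifestations of PASC, not exposure effects within groups. Propensity score matching, in the causal inference section, could yield risk differences, but none by subgroup is stated.

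**The case against.** The strongest objection is that this is an omission a full analysis plan may fill. The article does not commit to reporting odds ratios, does not name the GLMM link, and risk differences are post-estimation output. This stands in part: nothing stated has to be reversed. But the article does fix a rule on which interactions go forward, and that rule does not match the stated purpose.

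Three stronger readings are tempting, and the document does not support them.

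- A reader might infer that product terms are the only route to interactions. They are not: GPBoost and subgroup-specific analysis are also planned, although neither is stated to give an absolute contrast.
- A reader might infer that susceptible groups are discarded. The rule removes the interaction term. Main effects can stay, a high-risk group remains visible through its main effect, and absolute risks can still be derived from the fitted model.
- A reader might infer that equal odds ratios always mean a larger absolute effect in the higher-risk group. The last two rows of the table show that this can vanish or reverse.

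The Discussion's aim to "identify groups with greater susceptibility or resilience to PASC" also gives limited support. In context it concerns gender, education and marital status, which is mostly a question of main effects. The targeting aim rests better on the Introduction and on the Discussion's remarks on vulnerable populations.

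Finally, additive contrasts may be imprecise (31% to 47% power at OR 1.5), and with OR 1.2 at 20% vs 33.3% the gap is only about 1 point. Both are fair, and they argue for a short list with intervals rather than more tests.

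**Conclusion.** The point holds as a mismatch between the screening scale and the purpose. Interactions are retained by significance of product terms, on the odds-ratio scale in the logistic model and presumably in the GLMM, and no stated analysis reports how the absolute effect of an exposure differs between groups. A near-zero product term can hide a twofold difference in excess cases (82 vs 162 per 1,000 exposed at unexposed risks of 10% and 30% with OR 2). It can also go with no difference or a reversed one. Which applies here is unknown, because the document gives neither PASC risks nor exposure effects. The sizes rest on assumed risks, odds ratios and equal cells, and the power figures ignore clustering by city. This is a worthwhile low-cost improvement; the planned models themselves can stand.

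**What to change.** Name in advance a short list of exposures and subgroups. For each pair, report from the models already planned:

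- standardised PASC risks with and without the exposure in each subgroup;
- the risk difference in each subgroup;
- the contrast of risk differences (or RERI), with confidence intervals.

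Give these alongside the product term and whether or not it is significant. State the GLMM link. Add that a non-significant product term alone will not be taken to show that groups are equally affected.

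No new data or models are needed. The costs are two scales to explain, modest precision for the additive contrasts, and averaging over the city effects when risks are standardised. With only 14 cities, a plain cluster bootstrap may be unreliable, so the city-level uncertainty needs a method suited to few clusters.
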